## **8.3 Pregnancy**

Any pregnancy occurring in a female patient or a female partner of a male patient will be collected from the first study drug administration and until 28 days after the last study drug administration or patient EOS. Patients will also be instructed to notify the Investigator after completion of the safety FU or discontinuation from the study if she (for female patients) or the patient’s partner (for male patients) becomes pregnant within 3 months after the last study drug administration.

A patient who falls pregnant on study must be withdrawn from study treatment immediately.

Pregnancy should be reported to **Sponsor Drug Safety representative within 24 hours** of learning of its occurrence using a Clinical Pregnancy Form.

Sponsor Drug Safety representative will request a pregnancy case update every 3 months and within 2 weeks of the estimated delivery date. The pregnancy should be followed up to determine outcome, including spontaneous or voluntarily termination, details of the birth and the presence or absence of any birth defects, congenital abnormalities or maternal and/or new born complications. Pregnancy follow-up should be recorded on the same form and should include an assessment of the possible relationship to the study treatment of any pregnancy outcome. Any SAE experienced during pregnancy, as well as abnormal pregnancy outcomes (e.g. spontaneous abortion, fetal death, stillbirth, congenital anomalies and ectopic pregnancy) must be reported on the SAE Form.

The detailed procedure for reporting pregnancies is located in the Investigator File provided to each site.

## **8.4 Overdose**

An overdose is the accidental or intentional use of a study treatment in an amount higher than the planned dose being studied.

Definition of overdose: Any single dose of MP0317 that is  $\geq 10\%$  higher than the assigned dose.

In the event of an overdose, the Investigator should contact the Sponsor immediately and document the quantity of the excess dose as well as the duration of the overdosing in the eCRF. Decisions regarding any symptomatic treatment and/or study treatment interruptions or modifications will be made by the Investigator, in consultation with the Sponsor, based on the clinical evaluation of the patient. Overdose, per se, will not be reported as an AE/SAE although any resulting symptoms will be reported.

There is currently no known specific rescue medication for MP0317. If indicated, patients should be treated to control symptoms (e.g. hypertension, cardiac symptoms or dysfunction) with appropriate symptomatic measures (Sections 6.1 and 12.6). All medication used to control these symptoms should be recorded in the eCRF.

## 8.5 Dose Escalation Review Committee and Stopping Rules

A DERC, composed of all Principal Investigators, the Sponsor's medical and PK expert(s) and Drug Safety representative, an independent clinical expert and clinical research organization (CRO) representative(s), will meet to make recommendations based upon their review of patient tolerability and safety data (including DLTs, AEs, laboratory data and the BLRM summaries of DLT risk, if applicable) along with PK, pharmacodynamic and preliminary antitumor activity information available at the time of the decision. The ultimate decision remains with the Sponsor.

Administration at the next dose level cannot proceed until the Investigator receives written confirmation from the Sponsor indicating that the results of the previous dose level were evaluated and that it is safe to proceed to a higher dose level. If the MTD is not reached, the selected dose is that resulting in the predicted best therapeutic window for study treatment.

The composition, functioning (meeting frequency, data received etc.) and responsibilities of the DERC will be detailed in the DERC Charter (provided separately). All recommendations by the DERC, their rationale and decisions will be recorded in meeting minutes.

Unacceptable toxicities that may result in holding or closing enrollment will be considered when  $\geq 2$  patients in a dose escalation and/or safety expansion cohort, exhibit toxicities consistent with the definition of the same DLT per Section 5.2.5.

During the conduct of the study, any death that is considered possibly related to MP0317 will result in a study enrollment pause and, cessation of dosing equal to or higher than that dose level in which the death occurred, to allow for an expedited ad hoc evaluation by the DERC prior to further enrollment in the study.

## 9 STATISTICAL ANALYSES

The detailed methodology for summary and statistical analyses of the data collected in this study will be documented in a Statistical Analysis Plan (SAP). The SAP will provide all data handling rules, including the management of missing values and the handling of data for withdrawn patients. The SAP will also outline protocol deviation criteria. Any deviations from the planned analyses specified or populations defined within the SAP will be justified in writing and presented in the Clinical Study Report (CSR).

The clinical database lock will occur after all study data have been reconciled (i.e. 'cleaned') for all patients. The SAP for the study will be finalized and signed before the database lock.

Data will be analyzed and presented by dose level and study part. In all tables, listings and figures, the dose-escalation cohorts will be reported from the lowest to the highest dose and safety expansion data will be reported by indication/treatment arm.

### 9.1 Sample Size Determination

Up to 6 provisional dose levels are planned for this study with at least 1 to 3 patients per dose level. It is estimated that between 17 and 30 patients will be included for the dose-escalation part of the q3w schedule, and 12 to 18 patients for the dose-escalation part of the q1w schedule. Up to 15 patients treated at the RDE (or MTD) will be included in the safety expansion part of each dosing schedule giving a total of between 32 and 78 patients. The actual number of patients will depend on the number of dose levels/cohorts that are tested, the number of patients considered non-evaluable for the DDS and who are replaced, and the safety profile seen at each dose level.

### 9.2 Data Handling

#### 9.2.1 Screen Failures

Data will be listed including demography, reason for screen failure, eligibility criteria and any SAEs. These patients will not be part of any summary tables except for summarizing disposition.

#### 9.2.2 Missing Data and Treatment Discontinuation

Due to the dose-escalation design of the first part of the study, no imputation of missing values will be done for any analysis (except imputation for missing partial dates of AEs and concomitant medications). Reasons for discontinuation from the study treatment and study will be listed and summarized.

Additional patients will be included in the dose-escalation part of the study if fewer than 3 patients per dose level in cohort number 3 and higher are evaluable for DLT assessment. Patients in the safety expansion part will be replaced if they do not have at least one post-screening efficacy assessment and did not discontinue due to clinical PD.

### 9.3 Analysis Sets

#### 9.3.1 Safety Analysis Set

The safety analysis set (SAS) will consist of all patients who received at least one dose of MP0317 and had at least one post-dose safety assessment (where the statement that a patient had no AEs constitutes a safety assessment). The SAS will be the primary population for all demography, safety,

immunogenicity, efficacy and pharmacodynamic related endpoints, except for determination of the dose-DLT relationship.

### 9.3.2 Dose-Determining Set

The dose-determining set (DDS) will consist of all patients in the SAS, who meet the dose-limiting toxicity evaluability criteria in Sections 5.2.5 and 5.2.6. Patients who do not meet these minimum treatment and safety evaluation requirements will be regarded as ineligible for inclusion in the DDS and will be replaced if needed until the minimum number of patients required for evaluation is reached. The DDS will be used in the BLRM to estimate the dose-DLT relationship in the dose-escalation part of the study.

### 9.3.3 Pharmacokinetics Analysis Set

The PK set consists of all patients who received at least one dose of MP0317 and had at least one post-dose PK measurement.

## 9.4 Primary Analysis

### 9.4.1 Dose-Escalation

An adaptive BLRM guided by the EWOC principle will be used in the dose-escalation part to determine the RDE (or MTD). The use of Bayesian response adaptive models for phase 1 studies has been advocated by the European Medicines Agency (EMA) Guideline on Clinical Trials in small Populations and by Rogatko and is one of the key elements of the Food and Drug Administration (FDA)'s Critical Path Initiative.

#### 9.4.1.1 Dose-Finding of Single Agent MP0317

A 2-parameter BLRM will be used for dose-escalation. All information currently available about the dose-DLT relationship of MP0317 is summarized in a prior distribution (Table). This prior distribution is then updated after each cohort of patients with all of the DLT data available in the DDS from the current study. Once updated, the distribution summarizes the probability that the true rate of DLT for each dose lies in the following categories:

- [0,16%) underdosing
- [16%,33%) targeted toxicity
- [33%,100%] excessive toxicity

The EWOC principle mandates that any dose of MP0317 that has more than a 25% chance of being in the excessive toxicity category is not considered for the next cohort. After a clinical synthesis of the available toxicity information (including AEs that are not DLTs), PK, pharmacodynamic and efficacy information as well as the recommendations from the Bayesian model, the DERC will determine the dose level for the next cohort at a dose-escalation meeting. In all cases, where there is a change in dose level to be administered to the next enrolled patients, a new model will be defined using a Meta-Analytic-Predictive prior, based on the observed data.

The frequency of DLTs will be tabulated by dose for patients in the dose-escalation part and information about the DLTs will be listed by dose.

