#### 9.4.1.2 Bayesian Logistic Regression Model for MTD Determination

The objective of the design is to determine the MTD defined as the highest dose with less than 25% risk of the true DLT rate being above 33%. The dose-finding will be guided by a Bayesian 2-parameter logistic regression model with overdose control. These designs have been shown to be superior regarding the precision of MTD determination compared to 3+3 designs and have been particularly endorsed by the FDA.

The model is formulated as follows:

$$\text{logit}(p(d)) = \log(\alpha) + \beta \cdot \log(d/d^*),$$

where  $\text{logit}(p) = \log(p/(1-p))$ .  $p(d)$  represents the probability of having a DLT in the first cycle at dose  $d$ ,  $d^* = 1$  mg/kg is the reference dose, allowing for the interpretation of  $\alpha$  as the odds of a DLT at dose  $d^*$ , and  $\theta = (\log(\alpha), \log(\beta))$  with  $\alpha, \beta > 0$  is the parameter vector of the model. Standardized doses will be used such that one of the doses ( $d^*$ ) equals 1, e.g. doses are rescaled as  $d/d^*$ . As a consequence,  $\alpha$  is equal to the odds of the probability of toxicity at  $d^*$ .

Since a Bayesian approach is applied, a prior distribution  $\pi(\theta)$  for the unknown parameter vector  $\theta$  needs to be specified. This prior distribution will be specified as a normal distribution, i.e.

$$\pi(\theta) = \text{MVN}(\mu, \Sigma)$$

mean vector  $\mu$  and covariance matrix  $\Sigma$ , with

$$\Sigma_i = \begin{pmatrix} \sigma_{i,11}^2 & \sigma_{i,11}\sigma_{i,22}\rho_i \\ \sigma_{i,11}\sigma_{i,22}\rho_i & \sigma_{i,22}^2 \end{pmatrix}$$

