#### 9.4.1.3 Prior Derivation for Q3W

The starting dose of MP0317 will be 0.03 mg/kg, which is presumed to be at the lower end of the pharmacologically active dose range. No critical toxicities were observed in the cynomolgus monkey toxicity studies up to the maximum applied MP0317 dose level of 100 mg/kg. It is therefore highly unlikely that a severe toxicity defined as DLT in this study would occur at this starting dose, leading to the prior assumption that the median DLT rate at 0.03 mg/kg is 1%. On the other hand, assuming dose-proportionality in humans using a cautious approach, the median DLT rate at the highest planned dose = 10 mg/kg was therefore assumed to be 20%.

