## 9.13 Interim Analyses

Each dose-escalation step is considered to be an interim analysis. The BLRM will be updated with the respective number of patients treated and the number of DLTs observed in the last cohort. The updated model will then give a statistical recommendation for the next escalation step. In addition, a risk-benefit assessment that includes a comprehensive analysis of available safety and clinical information will be done to decide on the next escalation steps.

The SAP will describe the planned interim analyses in greater detail.

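### Sections 9.4.1.1 and 9.13 do not fix one rule for updating the BLRM at a dose change, Appendix 12.8 assessed no MAP step, and Table 23 misprints the prior intercept

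*Protocol*

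**What the plan says.** Protocol Section 9.4.1.1 summarises current knowledge in a prior and continues: "This prior distribution is then updated after each cohort of patients with all of the DLT data available in the DDS from the current study". Section 5.2.7.1 agrees, saying each recommendation draws on the full history of previous cohorts. The overdose rule in 9.4.1.1 is that a dose that "has more than a 25% chance of being in the excessive toxicity category is not considered for the next cohort".

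The same subsection then adds, for every case in which the next patients receive a different dose level, that "a new model will be defined using a Meta-Analytic-Predictive prior, based on the observed data". Section 9.13 describes each interim step in a third way: "The BLRM will be updated with the respective number of patients treated and the number of DLTs observed in the last cohort".

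On the prior itself, Section 9.4.1.3 assumes that "the median DLT rate at 0.03 mg/kg is 1"% and that "the median DLT rate at the highest planned dose = 10 mg/kg was therefore assumed to be 20"%. Section 9.4.1.2 sets the scale: 1 "mg/kg is the reference dose". Table 23 then gives the mean vector for (log α, log β) as -2.685; -0.594, with standard deviations 2; 0.5 and correlation 0. Table 24 lists the prior DLT probabilities, and Appendix 12.8 gives the data scenarios and operating characteristics on which Section 9.4.1.5 relies.

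**The concern.** The 25% limit on P(OD) is the model's overdose control, so the protocol has to fix which prior and which data produce P(OD). Here a fixed prior with all data, a MAP prior rebuilt from trial data at each dose change, and an update with the last cohort stand side by side without a link. If the MAP prior already contains the earlier cohorts and is then updated with all data in the dose-determining set, those patients count twice and the posterior is too narrow. A fixed 25% cut-off applied to a posterior of the wrong width can give a different escalation decision from the same observations.

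Table 23 is the only place where the prior parameters are given as numbers. If it is wrong, code written from it would not be the model that was assessed.

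**Working it through.** **1. Intercept and slope from the stated medians.** The model is logit p(d) = log α + β·ln(d/d*), with d* = 1 mg/kg. The inputs are 1% at 0.03 mg/kg and 20% at 10 mg/kg.

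- logit(0.20) = ln(0.25) = -1.3863; logit(0.01) = ln(0.01/0.99) = -4.5951; ln(10/0.03) = 5.8091.
- β = (-1.3863 + 4.5951)/5.8091 = 0.5524, and ln β = -0.594. Table 23 prints -0.594, so the slope is reproduced.
- log α = -1.3863 - 0.5524 × 2.3026 = -2.658. Table 23 prints -2.685, with the last two digits exchanged.

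**2. Which intercept produced Table 24?** At the reference dose the slope drops out, so P(OD) = 1 - Φ((logit 0.33 - mean)/2), with logit 0.33 = -0.708.

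- With -2.658: 1 - Φ(0.975) = 0.165.
- With -2.685: 1 - Φ(0.988) = 0.162.

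The other two doses need numerical integration over the prior:

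| Dose (mg/kg) | Table 24 P(OD) | Intercept -2.658 | Intercept -2.685 |
|---|---|---|---|
| 1.00 | 0.166 | 0.165 | 0.162 |
| 3.00 | 0.267 | 0.267 | 0.263 |
| 10.00 | 0.401 | 0.401 | 0.396 |

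Table 24 was computed with -2.658. The largest gap between the two columns is 0.401 - 0.396 = 0.005. The same two doses exceed 0.25 either way.

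**3. Which updating rule produced Table 30?** P(OD) was recomputed by grid integration with intercept -2.658, the fixed prior and each patient counted once:

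- Setting 1 scenario 5, next dose 10 mg/kg: 0.086 (Table 30: 0.084).
- Setting 2 scenario 4, at 3.00 mg/kg: 0.305 (Table 30: 0.306).
- Setting 4a scenario 3, at 3.00 mg/kg: 0.239 (Table 30: 0.242).
- Setting 4a scenario 5, at 10 mg/kg: 0.244 (Table 30: 0.244).

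Doubling all data would give 0.037 in the first case. Doubling only the earlier cohorts would give 0.235 in the second and 0.363 in the third. Appendix 12.8 mentions no MAP step.

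**4. What double use would do.** Assumption: the MAP prior carries the cohorts before the current one at full weight, and those cohorts enter the likelihood again.

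| Data | Dose judged (mg/kg) | Counted once | Earlier cohorts doubled | 25% limit |
|---|---|---|---|---|
| Setting 2 scenario 4: 0/3 at 0.03, 0.10 and 0.30; 1/3 at 1.00 | 3.00 | 0.305 | 0.235 | barred → allowed |
| Setting 4a scenario 3: 0/3 at 0.03 and 0.10; 1/3 at 0.30; 0/3 at 1.00 | 3.00 | 0.239 | 0.363 | allowed → barred |

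The first row crosses 0.25 at a total weight of roughly 1.75 on the earlier cohorts (P(OD) 0.248). If the current cohort were doubled as well, that row would rise to about 0.40 instead.

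An enumeration of 1,452 dose checks (3 or 6 patients per dose, all data doubled) moved 50 from barred to allowed and 31 from allowed to barred.

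**5. What the printed intercept would do.** With each patient counted once, using -2.685 in place of -2.658 moved none of the same 1,452 checks from barred to allowed.

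**The case against.** The strongest defence is that double use is nowhere stated. The sentence about all data refers to the Table 23 prior, and the MAP sentence does not say the new model is refitted to the patients who shaped its prior. Read with 9.13, a prior carrying the earlier cohorts plus the last cohort alone counts each patient once. If that prior is simply the carried-forward posterior, the result is mathematically the same as the fixed prior with all data. This stands: double use is one possible reading, and 9.13 alone need not contradict 9.4.1.1. But a MAP prior is not in general the carried-forward posterior, and nothing says which is meant.

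A reader might infer that the 25% limit is systematically weakened. The documents do not support this. Doubling earlier DLT-free cohorts loosens the limit, but doubling a cohort with a DLT can tighten it, as the second row of the table shows. Full weight is also the extreme case, since a MAP prior that allows for heterogeneity discounts the earlier data.

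A reader might also infer that the wrong intercept endangers patients. Table 24 shows the assessed model used -2.658, and nothing indicates that -2.685 was ever coded.

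Other safeguards exist: the general 3.33-fold cap on escalation, the review committee's clinical synthesis, and the sponsor's written confirmation. They limit the consequences but do not settle how P(OD) is computed. Section 9.13 leaves further interim detail to the SAP, which is not at hand. That does not remove the inconsistency, because the protocol itself states the q3w rule.

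**Conclusion.** The point holds in two parts.

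First, the protocol states updating rules for the q3w model that are not reconciled and that can give opposite escalation decisions on the same data. The shifts of 0.305 to 0.235 and 0.239 to 0.363 assume full-weight borrowing with the earlier cohorts doubled; a discounted MAP prior would lie between the two figures in each pair. The defect is misplaced precision that can act in either direction. The favourable assessment in Section 9.4.1.5 and Appendix 12.8 applies to a fixed prior with each patient counted once and does not extend to a MAP step.

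Second, the intercept in Table 23 is a transposition of -2.658. Its effect on P(OD) is at most about 0.005 and it changed no decision among the cases checked. It needs correcting because it is the printed specification of the prior, not because it alters dosing.

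**What to change.** - State one updating rule for the q3w schedule in which each patient's data enter once: either the fixed Table 23 prior plus all data in the dose-determining set, as assessed in Appendix 12.8, or the equivalent carried-forward posterior plus the new cohort. Word 9.4.1.1 and 9.13 the same way.
- Remove the MAP sentence for dose changes within a schedule. If a MAP prior is intended, define it so that no data are reused, and rerun the data scenarios and operating characteristics with it.
- Correct Table 23 to -2.658; -0.594 and confirm that the production code uses that value.

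Without a MAP prior, the cost is a few lines of text, one number and a code check. Keeping it adds a new set of simulations.

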#### 9.4.1.2 Bayesian Logistic Regression Model for MTD Determination

The objective of the design is to determine the MTD defined as the highest dose with less than 25% risk of the true DLT rate being above 33%. The dose-finding will be guided by a Bayesian 2-parameter logistic regression model with overdose control. These designs have been shown to be superior regarding the precision of MTD determination compared to 3+3 designs and have been particularly endorsed by the FDA.

The model is formulated as follows:

$$\text{logit}(p(d)) = \log(\alpha) + \beta \cdot \log(d/d^*),$$

where  $\text{logit}(p) = \log(p/(1-p))$ .  $p(d)$  represents the probability of having a DLT in the first cycle at dose  $d$ ,  $d^* = 1$  mg/kg is the reference dose, allowing for the interpretation of  $\alpha$  as the odds of a DLT at dose  $d^*$ , and  $\theta = (\log(\alpha), \log(\beta))$  with  $\alpha, \beta > 0$  is the parameter vector of the model. Standardized doses will be used such that one of the doses ( $d^*$ ) equals 1, e.g. doses are rescaled as  $d/d^*$ . As a consequence,  $\alpha$  is equal to the odds of the probability of toxicity at  $d^*$ .

Since a Bayesian approach is applied, a prior distribution  $\pi(\theta)$  for the unknown parameter vector  $\theta$  needs to be specified. This prior distribution will be specified as a normal distribution, i.e.

$$\pi(\theta) = \text{MVN}(\mu, \Sigma)$$

mean vector  $\mu$  and covariance matrix  $\Sigma$ , with

$$\Sigma_i = \begin{pmatrix} \sigma_{i,11}^2 & \sigma_{i,11}\sigma_{i,22}\rho_i \\ \sigma_{i,11}\sigma_{i,22}\rho_i & \sigma_{i,22}^2 \end{pmatrix}$$

#### 9.4.1.3 Prior Derivation for Q3W

The starting dose of MP0317 will be 0.03 mg/kg, which is presumed to be at the lower end of the pharmacologically active dose range. No critical toxicities were observed in the cynomolgus monkey toxicity studies up to the maximum applied MP0317 dose level of 100 mg/kg. It is therefore highly unlikely that a severe toxicity defined as DLT in this study would occur at this starting dose, leading to the prior assumption that the median DLT rate at 0.03 mg/kg is 1%. On the other hand, assuming dose-proportionality in humans using a cautious approach, the median DLT rate at the highest planned dose = 10 mg/kg was therefore assumed to be 20%.

**Table 23. Summary of Prior Distribution**

| Mean Vector    | STD Vector | Correlation |
|----------------|------------|-------------|
| -2.685; -0.594 | 2; 0.5     | 0           |

STD, standard deviation.

A summary of the prior probabilities of DLT at different doses, as well as the corresponding probability of under, targeted and overdosing, are shown in Table 24. Graphically, the prior medians with accompanying 95% credible intervals (CrI) are shown in Figure 3. The uncertainty around the medians is large, showing the low amount of in-human information this prior provides.

